### Follow-up

Adverse effects will be classified according to the international Common Terminology Criteria for Adverse Events v 5.0/CTCAE document.

A follow-up phone-call will be performed once a week for the first 4 weeks after SBRT.

Regular cardiological follow-up visits, including 12-lead ECG and ICD interrogation, will be performed 3, 6, and 12 months after SBRT. Echocardiography examination and SF-36 health questionnaire will be provided 3, 6, and 12 months after SBRT. Patients will be visited by a radiation oncologist, and thorax CT will be performed 3 and 12 months after SBRT.

Pharmacological therapy, including antiarrhythmic drugs, will be maintained the same as before SBRT during the entire follow-up.

With regard to the early post-SBRT phase and the possible occurrence of transient processes impacting on cardiac arrhythmogenicity, accordingly to literature [16–18, 21], a 6-week “blanking period,” starting immediately after SBRT treatment, will be considered in the analysis of VT recurrences during follow-up.

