### Endpoints of the study

#### Primary endpoints

Two primary endpoints of the study have been defined, represented by safety and efficacy of the treatment, respectively.Primary safety endpoint is to evaluate the safety of radiation therapy in the acute phase (during the first 30 days of the procedure) and at 3, 6, and 12 months. The incidence of serious adverse events related, or presumably related, to radioablation will be assessed as a percentage of the enrolled patients. Serious adverse events were the following:DeathCardio-circulatory arrestAcute myocardial infarctionCardiogenic shockPericarditis, myocarditis, and/or endocarditisAcute heart failureGastro-esophageal lesion (ulcer/stenosis/fistula/hemorrhage/perforation)Bronchopulmonary infectionInjury to the respiratory system (fistula/bronchial or tracheal stenosis, pulmonary fibrosis)Radio-induced oncogenesisPrimary efficacy endpoint is to evaluate the procedural effectiveness of therapy at 3, 6, and 12 months, represented by the total number of VT/VF episodes occurring after “blanking period,” compared with the period preceding the radioablation procedure (6 months).

VT episodes will be categorized as follows:VT episode > 30 s, regardless of the intervention of the ICDVT episode conditioning ICD intervention by means of “anti-tachycardia pacing” electrical therapy (without shock delivery)VT episode conditioning ICD shock intervention

The 6-week “blanking period” will start on the procedure day.

As a rule, pharmacological therapy, including antiarrhythmic drugs, will be maintained the same as before SBRT during the follow-up period. Changes of the pharmacological therapy will be determined only by specific clinical reasons.

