#### Calculation of the target sample size and statistical analysis

A sample of 15 patients will allow a 60% reduction in ventricular arrhythmic episodes to be assessed as significant (*p* < 0.05), assuming an average of 10 episodes in the 3 months preceding the procedure, with a statistical power of 90%. Continuous variables will be expressed as mean ± standard deviation or median and interquartile range variables with non-normal distribution, and discrete variables as absolute numbers and percentages. Primary efficacy endpoint (reduction of ventricular arrhythmic episodes) and secondary endpoints (clinical, echocardiographic, and psychometric characteristics) will be evaluated with the Student’s *t* test for paired data (continuous variables with normal distribution) or with the Wilcoxon sign rank test (variables with non-normal distribution). Kaplan-Meyer curves will be developed for event-free survival analysis at follow-up. All tests will be two-tailed and a *p* < 0.05 will be considered significant.

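### The primary efficacy comparison sets unscaled VT/VF counts over unequal windows against a 6-month baseline, so an unchanged rate reads as a 73% fall at 3 months

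*Protocol article*

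**What the plan says.** Under Primary endpoints, the Protocol article sets out to "evaluate the procedural effectiveness of therapy at 3, 6, and 12 months". The measure is "represented by the total number of VT/VF episodes occurring after" the blanking period, and it is "compared with the period preceding the radioablation procedure (6 months"). The same section fixes the start of blanking: "The 6-week “blanking period” will start on the procedure day". The Follow-up section confirms that this period "will be considered in the analysis of VT recurrences during follow-up".

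The section on sample size and statistical analysis names the paired Student's t test or, for non-normal data, the Wilcoxon signed-rank test, two-sided at 0.05. On size it says: "A sample of 15 patients will allow a 60% reduction in ventricular arrhythmic episodes to be assessed as significant", with 90% power, "assuming an average of 10 episodes in the 3 months preceding the procedure".

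None of these sections mentions a rate, scaling by observation time, or a baseline window matched to the follow-up window. The article does not say whether the 6- and 12-month counts accumulate from the end of blanking or cover separate intervals.

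**The concern.** A count depends on how long one counts. The baseline covers 6 months, while the first follow-up reading covers only what is left of 3 months after 6 weeks are removed. Neither planned test corrects for this, so the shorter window alone produces fewer episodes. At the later readings the distortion may shrink, vanish or reverse, depending on how the windows are formed. The three readings of one endpoint can then disagree for purely arithmetic reasons.

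The study has a single arm, so the before-after comparison is its only evidence of efficacy. The Conclusions section links reaching the primary endpoints to offering the treatment more widely. The most inflated reading, at 3 months, also matures first.

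**Working it through.** **Inputs from the Protocol article.** Baseline 6 months; blanking 6 weeks = 42 days; readings at 3, 6 and 12 months; 15 patients; 60% reduction; mean of 10 episodes in 3 months; power 90%; two-sided 0.05.

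**The plan's own figure.** The 15 patients cannot be reproduced because no standard deviation is given. A fall from 10 to 4 is a difference of 6. With 15 pairs and an exact paired t test, 90% power needs a standard deviation of the difference of about 6.7 episodes. The calculation also uses a 3-month baseline, not the 6-month one in the endpoint.

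**Window lengths.** 42 / 30.44 = 1.38 months. If counts are cumulative from the end of blanking:

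- 3 months: 3 − 1.38 = 1.62; 1.62 / 6 = 0.27
- 6 months: 6 − 1.38 = 4.62; 4.62 / 6 = 0.77
- 12 months: 12 − 1.38 = 10.62; 10.62 / 6 = 1.77

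If intervals are separate, the windows are 1.62, 3 and 6 months, with ratios 0.27, 0.50 and 1.00.

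**Apparent change.** At a constant underlying rate, apparent reduction = 1 − RR × (window / 6), where RR is the true rate ratio.

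| Reading | Cumulative, RR = 1 | Cumulative, RR = 0.4 | Separate, RR = 1 | Separate, RR = 0.4 |
|---|---|---|---|---|
| 3 months | 73% fall | 1 − 0.4 × 0.27 = 89% fall | 73% fall | 89% fall |
| 6 months | 23% fall | 1 − 0.4 × 0.77 = 69% fall | 50% fall | 1 − 0.4 × 0.50 = 80% fall |
| 12 months | 77% rise | 1 − 0.4 × 1.77 = 29% fall | no change | 60% fall |

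In episodes, 10 per 3 months is 20 per 6 months. With no effect, the 3-month reading expects 20 × 0.27 = 5.4 against 20.

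**Break-even at 12 months, cumulative.** The count rises when RR × 1.77 > 1, so any true reduction below 1 − 6 / 10.62 = 43.5% looks like an increase.

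**Would the 3-month baseline of the sample-size statement help?** 1.62 / 3 = 0.54, so an unchanged rate would still show a 46% fall. Neither stated baseline matches the first window.

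**Error rates (simulation; the variability is assumed).** Gamma-Poisson counts, 15 patients, mean of 20 episodes per 6 months. Between-patient CV is 0.5–1.5 and period-to-period CV 0.5–1.0, because the article gives no variance. Only significant results in the direction of benefit are counted.

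- No effect, 3 months, raw counts: Wilcoxon declares a reduction in roughly 55–100% of trials, paired t in about 27–100%. On rates, Wilcoxon gives about 2–4%.
- True 60% cut, 12 months, cumulative: Wilcoxon power is about 8–32% on raw counts against 35–97% on rates. With no period-to-period variation, raw-count power rises to about 72–92%.

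**The case against.** The best defence is that this is a condensed article and an analysis plan not shown may scale by observation time. The article names a quantity and a reference period; it does not say outright that unscaled counts enter the test. That is fair as a caution: a reader should not infer that a raw-count analysis will certainly be run. But the endpoint as worded is a total set against a period of stated, different length. A plan that divided by time would be changing the endpoint, not filling in detail.

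A second objection stands in full. A reader might infer that an effective treatment will fail at 12 months. The article does not support this. It rests on cumulative counting, which is not stated; with separate intervals the last window is 6 months and matches the baseline. Even under cumulative counting, a true 60% cut still shows a 29% fall, and whether that reaches significance depends on variability the article does not give. The period CVs of 0.5–1.0 used above are noisier than the planning implies: with both CVs at 0.5, the standard deviation of the difference over 3 months is about 7.7, against the 6.7 needed for 15 patients. Part of the low power therefore comes from assumed noise; power on rates is itself only 35% at the noisiest setting.

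Third, scaling is not a complete cure. The Eligibility criteria select patients for recurrent or incessant VT, so rates may fall after enrolment without any treatment effect. That also stands.

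**Conclusion.** The point holds. The firm part is the 3-month comparison: an unchanged VT rate reads as a 73% reduction, larger than the 60% target, under either reading of the windows. It needs only a constant underlying rate and no assumption about variance.

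The 6- and 12-month distortions are conditional. Cumulative counting gives a null 23% fall and 77% rise, and hides any true reduction below about 43.5% at 12 months. Separate intervals give 50% and 0%. The simulated error rates illustrate direction and rough size under assumed CVs and should not be quoted as properties of this trial. The claim that the trial cannot show a true 60% cut at 12 months is not supported.

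This should be corrected before analysis: it is a stated rule that misleads if followed as written.

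**What to change.** - Define the primary efficacy endpoint as VT/VF episodes per device-monitored month. Baseline: episodes in the 6 months before SBRT divided by monitored months. Follow-up: episodes from the end of blanking to each time point divided by monitored months.
- State whether the 6- and 12-month windows are cumulative or separate.
- Run the paired test on these rates, or fit a count model with log monitored time as offset. Report the rate ratio with its 95% CI.
- Reconcile the 6-month baseline in the endpoint with the 3-month baseline in the sample-size statement.
- Note in the interpretation that scaling does not deal with regression to the mean.

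The cost is a few sentences in the endpoint and analysis sections. ICD interrogation and remote monitoring after SBRT are already planned. The one item to check is monitored time before SBRT: the Eligibility criteria require an ICD but not six months of device history, so baseline monitored months must be recorded for each patient. Dividing by monitored time also prevents follow-up cut short by death or dropout from lowering counts and passing for benefit.

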#### Secondary endpoint

Secondary endpoints are the following:Global mortality during follow-up (up to 12 months)Variations in the quality of life of patients in the follow-up (up to 12 months) with respect to the basal conditionChanges in cardiac function assessed by estimating the ejection fraction of the left ventricle on the echocardiographic examination in the follow-up (up to 12 months)

### Statistical planning

#### Stopping criteria for ending the study

A study stopping rule based on the global rate of serious adverse events occurring within 30 days from the date of SBRT, that may be a consequence of the radioablation treatment (death, acute myocardial infarction, cardiogenic shock, cardio-circulatory arrest), will be adopted after enrollment of 5 patients. This rule will require the interruption of enrollment in the study if the observed adverse event rate will be higher than expected based on the data reported in the literature (at the time of study design) [12, 17–20]. Specifically, the reported rate (0 events out of 12 patients) is compatible with an estimated maximum frequency of 1 out of 5 events (upper limit of the 95% confidence interval). Therefore, the study will be stopped if ≥ 2 events occur within 30 days of the treatment carried out, among the first 5 patients treated.

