## Methods

The STRA-MI-VT trial was designed as spontaneous, experimental (phase Ib/II), prospective, open-label study. Fifteen patients are expected to be enrolled. The design of the study is illustrated in Fig. 1 and in Table 1.

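### The only numeric stopping threshold shown covers the first 5 treated patients, detects high event rates weakly, and is triggered by enrolment although it counts 30-day events after treatment

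*Protocol article*

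**What the plan says.** All the relevant text is in the protocol article, under Stopping criteria for ending the study, unless another section is named.

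- **Events counted:** those that may result from radioablation ("death, acute myocardial infarction, cardiogenic shock, cardio-circulatory arrest"), within 30 days of treatment.
- **Principle:** enrolment is interrupted "if the observed adverse event rate will be higher than expected based on the data reported in the literature".
- **Basis:** no events in 12 published patients, a result which, according to the plan, "is compatible with an estimated maximum frequency of 1 out of 5 events (upper limit of the 95% confidence interval"). Neither the interval method nor its sidedness is given.
- **Threshold:** "the study will be stopped if ≥ 2 events occur within 30 days of the treatment carried out, among the first 5 patients treated".
- **Timing:** the rule "will be adopted after enrollment of 5 patients".
- **Size of the trial:** "Fifteen patients are expected to be enrolled" (Methods), over two years (Abstract; Study organization and status).

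**The concern.** The principle has no end point, but the only number that puts it into effect stops at the fifth treated patient. Ten of the 15 planned patients, two thirds of the trial, come after it. One event in the first 5 followed by five events in the next 5 would be 6 of 10, three times the plan's own maximum of 1 in 5, and would cross no stated threshold.

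A look at 5 patients also has little power to detect a bad event rate. That would matter less if later looks followed, but none is shown.

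Finally, the trigger and the count do not match. The rule takes effect when 5 patients are enrolled, but it counts events to day 30 in the first 5 treated. Table 1 places enrolment and the pre-treatment work-up before radioablation, so the 30-day data cannot exist when the fifth patient enrols. No hold on the sixth patient is written.

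At stake is how many patients are exposed before an excess of death, infarction, shock or arrest leads to a halt.

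**Working it through.** **Inputs from the article.** 0 of 12 published events; a limit of 1 in 5; a threshold of 2 in the first 5 treated; a 30-day window; 15 patients in 24 months.

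**Assumptions made here.** True event rates p from 5% to 60%, none of which the article gives as a true rate for this trial; independent patients; each patient counted at most once; a second look at 10 as an illustration.

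**Step 1: the plan's limit for 0 of 12.**

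- Exact two-sided: 1 − 0.025^(1/12) = 26.5%
- Exact one-sided: 1 − 0.05^(1/12) = 22.1%
- Wilson two-sided: 3.84/15.84 = 24.2%; Wilson one-sided: 18.4%
- Jeffreys two-sided: 18.5%
- Uniform prior: 20.6% one-sided, 24.7% two-sided
- Rule of three: 3/12 = 25.0%

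The plan's 1 in 5 is reproduced as a rounded value of the one-sided exact limit. In 5 patients the exact limits correspond to 5 × 0.221 = 1.10 and 5 × 0.265 = 1.32 events. Under either one, 1 of 5 (20%) is not above the limit and 2 of 5 (40%) is, so the threshold of 2 follows from both.

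**Step 2: the written rule.** P(stop) = 1 − (1−p)^5 − 5p(1−p)^4.

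At p = 0.40: 1 − 0.0778 − 0.2592 = 0.663. A 40% rate therefore passes with probability 0.337.

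**Step 3: the same criterion applied again at 10.** An observed rate above 1 in 5 means 3 or more of 10. With X the events in patients 1 to 5 and Y those in patients 6 to 10:

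P(stop) = P(X≥2) + P(X=0)·P(Y≥3) + P(X=1)·P(Y≥2).

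At p = 0.40: 0.6630 + 0.0778 × 0.3174 + 0.2592 × 0.6630 = 0.6630 + 0.0247 + 0.1719 = 0.860.

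| True rate | Stop, look at 5 only | Stop, looks at 5 and 10 |
|---|---|---|
| 5% | 2.3% | 2.8% |
| 10% | 8.1% | 11.3% |
| 20% | 26.3% | 38.9% |
| 30% | 47.2% | 66.9% |
| 40% | 66.3% | 86.0% |

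With the look at 5 only, the probability is 81.3% at a true 50% and 91.3% at 60%.

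**Step 4: timing.** Fifteen patients in 24 months is one per 730/15 = 49 days. On average the fifth patient's day 30 falls before the sixth arrives, but intervals between patients vary and the text does not require the wait.

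**The case against.** **The limit.** A reader might infer that the upper limit is wrong, because the exact two-sided value is 26.5%. The article does not support that. It names no method or sidedness, common variants fall on both sides of 20%, and the one-sided exact value rounds to 1 in 5. The two-tailed convention under Calculation of the target sample size and statistical analysis is written for tests, not for this interval. Using 26.5% would leave the threshold at 2 of 5. What remains is a request to label the figure.

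**Other safeguards.** A reader might also infer that this rule is the only formal protection and that patients 6 to 15 are unmonitored. An article condenses a protocol that is not shown, and board oversight or continuous review of serious events may be set out there. The article itself follows every patient for safety at 30 days and at 3, 6 and 12 months, and the general principle is not limited to 5 patients. The phrase about adoption after 5 could mark a starting point. This objection stands against any claim of no protection. It does not supply the missing number: the article derives its rule step by step and ends with a threshold confined to the first 5.

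**Choice of rates.** The 40% rate is an assumption, although it equals the rule's own boundary of 2 in 5. The plan regards 1 in 5 as compatible with the literature, so more stopping at a true 20% is not clearly a gain. The case rests on 30% and 40%, and the cost should be shown at 10% as well as 5%. Low sensitivity is unavoidable with 5 patients, which is a reason for looking again.

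**Timing.** At the planned pace an overlap is possible rather than expected, so this is a gap in wording with a modest practical risk.

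**Conclusion.** The point holds in this form: the only numeric threshold shown does not carry through the rule's own principle beyond the fifth treated patient. By itself it stops with probability 47% at a true rate of 30% and 66% at 40%. Its trigger (enrolment) does not match its count (30 days after treatment).

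The binomial results are exact, given independent patients each counted once. If two events in one patient, such as arrest followed by death, counted as two, stopping would be more likely than shown; the article does not say how such a case is counted. The true rates are assumptions.

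The documents do not establish that the limit for 0 of 12 is mis-stated, or that later patients lack every other safeguard.

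**What to change.** 1. Apply the same criterion, an observed rate above the stated literature limit, to the cumulative treated patients at least once more, for example 3 or more of 10. A look at 10 is one option among several; what matters is a written threshold beyond patient 5.
2. Read the first look when the fifth treated patient reaches day 30 and before the sixth is treated, and word the trigger in terms of treated patients.
3. State the operating characteristics, as in the table above.
4. As a minor point, name the method and sidedness of the limit for 0 of 12 (22.1% exact one-sided, 26.5% exact two-sided). The threshold of 2 in 5 is the same under either.

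The cost is a short amendment, a possible brief wait, and a small rise in false stops: 2.3% to 2.8% at a true 5%, and 8.1% to 11.3% at 10%. Only 4 patients had been treated when the article was submitted (Study organization and status), so at that point the first look had not been reached.

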#### Calculation of the target sample size and statistical analysis

A sample of 15 patients will allow a 60% reduction in ventricular arrhythmic episodes to be assessed as significant (*p* < 0.05), assuming an average of 10 episodes in the 3 months preceding the procedure, with a statistical power of 90%. Continuous variables will be expressed as mean ± standard deviation or median and interquartile range variables with non-normal distribution, and discrete variables as absolute numbers and percentages. Primary efficacy endpoint (reduction of ventricular arrhythmic episodes) and secondary endpoints (clinical, echocardiographic, and psychometric characteristics) will be evaluated with the Student’s *t* test for paired data (continuous variables with normal distribution) or with the Wilcoxon sign rank test (variables with non-normal distribution). Kaplan-Meyer curves will be developed for event-free survival analysis at follow-up. All tests will be two-tailed and a *p* < 0.05 will be considered significant.

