#### Eligibility criteria

The inclusion criteria are as follows:Patients with relapsing VT (at least 3 episodes of VT conditioning ICD intervention or VT with incessant or similar-incessant presentation) that has proved to be refractory to any form of pharmacological or non-pharmacological treatmentPatients with contraindication to conventional ablation, in relation to the high risk associated with the procedure for the type/severity of the condition of heart disease and/or presence of severe comorbidity; or alternatively, patients who have already undergone RF ablation in presence of an arrhythmogenic substrate refractory to previous ablation procedures or not suitable for any interventional approach,^1^ refusing any surgical ablative attempt because of a proven high operative risk, in relation to the patient’s characteristicsEjection fraction of the left ventricle ≥ 20%Age ≥ 50 yearsICD/subcutaneous ICD recipientsSigned informed consent

The exclusion criteria are as follows:Inability to express informed consent to participate in the studyPrevious thoracic radiotherapy with cardiac involvementActive myocardial ischemiaCardiac revascularization < 120 days.Non-correctable hemodynamic instability (cardiogenic shock, New York Heart Association (NYHA) IV)Comorbidity with prognosis < 12 months or other contraindications deemed significantPregnant women

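### The 90% power is stated for a 3-month baseline count, but the primary efficacy endpoint compares post-blanking totals at three time points with a 6-month baseline

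*Protocol article*

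**What the plan says.** **Power statement** (section Calculation of the target sample size and statistical analysis). The claim for the design is "A sample of 15 patients will allow a 60% reduction in ventricular arrhythmic episodes to be assessed as significant". The planning values behind that claim follow in the same sentence: "assuming an average of 10 episodes in the 3 months preceding the procedure, with a statistical power of 90" per cent. The t test and the Wilcoxon test are both provided for, depending on the distribution: "test for paired data (continuous variables with normal distribution) or with the Wilcoxon sign rank test (variables with non-normal distribution". The significance rule reads "All tests will be two-tailed and a *p* < 0.05 will be considered significant". No SD of the within-patient change is given.

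**Endpoint** (section Primary endpoints). Efficacy is assessed at 3, 6 and 12 months by the total number of VT/VF episodes once blanking is over. The reference for that total is given as "compared with the period preceding the radioablation procedure (6 months". Both that section and Follow-up set the blanking period at 6 weeks, starting with the procedure.

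**Population and numbers.** Planned enrolment is 15, the same figure as in the power statement. Mortality up to 12 months is a secondary endpoint. Eligibility covers "at least 3 episodes of VT conditioning ICD intervention or VT with incessant or similar-incessant presentation".

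**The concern.** The two sections disagree on the baseline window: 3 months in the power statement, 6 months in the endpoint. The power statement also mentions neither the blanking period nor which of the three time points the 90% refers to. A reader would take 90% as the chance that the trial's main efficacy test detects a 60% reduction, but the comparison behind that figure is not the one defined as the endpoint.

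The gap matters because the endpoint is worded as a total number and the windows differ in length. If raw totals are compared, the size and even the direction of the apparent change depend on which visit is used. An early total could look like success without any effect, and a late total could hide a real one. A single power figure cannot describe all three comparisons.

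**Working it through.** **Inputs from the article:** n = 15; 10 episodes in 3 months; 60% reduction; two-sided 0.05; 6-month baseline; 6-week (42-day) blanking period; time points at 3, 6 and 12 months. **Assumed, because the article gives no value:** the SD of within-patient change and the number of evaluable pairs.

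**1. The plan's own figure.** The drop is 10 × 0.60 = 6 episodes. For a two-sided paired t test with 15 pairs (14 df, noncentral t), 90% power needs a standardised change of 0.901. The largest SD of change that allows it is 6 / 0.901 = 6.66. The 90% can therefore be neither reproduced nor refuted from the article; it can only be turned into this condition.

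**2. Counted windows.** With a month of 365.25/12 = 30.44 days, 42 days is 1.38 months. The windows after blanking are 3 − 1.38 = 1.62, 6 − 1.38 = 4.62 and 12 − 1.38 = 10.62 months.

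**3. Totals under the endpoint as worded.** The assumed rate is 10/3 = 3.33 per month, so the 6-month baseline is 20. Follow-up total = 3.33 × window, multiplied by 0.4 under a true 60% cut.

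| Time point | Window (months) | Total, no effect | Change from 20 | Total, true 60% cut | Change from 20 |
|---|---|---|---|---|---|
| 3 months | 1.62 | 5.4 | −73% | 2.2 | −89% |
| 6 months | 4.62 | 15.4 | −23% | 6.2 | −69% |
| 12 months | 10.62 | 35.4 | +77% | 14.2 | −29% |

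At 3 months, a treatment with no effect already shows more than the 60% reduction on which the power is based.

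**4. Power at 12 months on totals.** The mean change is 20 − 14.16 = 5.84. Doubling the SD limit in step 1 for a 6-month count gives 2 × 6.66 = 13.3. Then 5.84 / 13.3 = 0.44, and 15 pairs give about 35% power. The 13.3 is an assumption; at SD 10 the same calculation gives 56%, and at SD 20 it gives 18%.

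**5. The same comparison on rates.** Per month, 3.33 falls to 1.33, a change of 2.00. With the SD scaled to 6.66 / 3 = 2.22, the standardised change is 0.90 and power returns to 90%. The loss in step 4 thus comes from comparing totals over unequal windows; a 6-month baseline does not by itself reduce power.

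**6. Sensitivity of the 3-month figure (paired t, drop of 6).** With 15 pairs, power is 90% at SD 6.66, 77% at SD 8, 58% at SD 10 and 30% at SD 15. At SD 6.66, 12 pairs give 81% and 10 give 72%. Pure Poisson counts would have SD √(10 + 4) = 3.74 and power above 99.9%.

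**The case against.** **The paired-t limit is not a limit on the trial.** A reader might infer from step 6 that the 90% fails once the SD of change exceeds about 6.7. The documents do not support that. The plan also provides for the Wilcoxon signed-rank test when data are not normal, which is likely for counts in a population running from a few treated episodes to incessant VT. In simulated skewed counts (gamma-Poisson, 15 patients, the same 60% reduction in everyone), Wilcoxon power was about 97% and t-test power about 82% at an SD of change of 9.8. When the effect also varied widely between patients (SD about 11.3), the figures were about 80% and 60%. The dispersion in these simulations is assumed, but they show that 90% can hold above SD 6.7. This objection stands, so 6.66 serves only as sensitivity.

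**The missing SD may be elsewhere.** An article commonly leaves variance assumptions to the full protocol or analysis plan. This stands too: the absent SD is not the finding.

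**Loss of pairs is inferred.** The text does not say that 15 complete pairs are assumed, and it gives no attrition rate. The 10 and 12 pair figures are illustrations.

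**The sponsor may intend rates.** If so, the 73%, 23% and 29% figures disappear and, as step 5 shows, power need not suffer. But the endpoint is worded as a total, and neither section mentions time adjustment. An analysis plan could add an SD or a rate, yet the two published statements would still disagree on the baseline window and leave the powered time point open.

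**Conclusion.** The point holds as a mismatch between the power statement and the endpoint. The 90% belongs to a 60% reduction from a 3-month count of 10; the written endpoint uses a 6-month baseline, post-blanking totals and three time points, none of which is named as the powered one.

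Taken literally as totals, and at the article's own assumed rate, no effect gives falls of 73% at 3 months and 23% at 6 months, while a true 60% rate cut gives only 29% at 12 months. These percentages rest on a constant episode rate and full follow-up. The 12-month power of about 35% also rests on an assumed SD of 13.3 and the paired t test.

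The stronger reading, that 90% is an arithmetic error, is not established: without an SD it can be neither confirmed nor rejected. Nor do the documents support any particular replacement figure or range.

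**What to change.** Reconcile the Primary endpoints section and the sample size section:

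- name one baseline window and one primary time point, and treat the other time points as supportive;
- define the comparison as episodes per month, with the 6-month baseline against follow-up after the blanking period;
- restate the power at n = 15 for that comparison and for the test that will be used, giving the SD or dispersion and the expected number of evaluable pairs behind it.

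If the dispersion is uncertain, give power over a stated range of values computed for the chosen test.

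The cost is some rewording and possibly a less favourable power figure. No extra patients or data collection are needed, since the 6-month baseline is already part of the endpoint.
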